#### **2.4.5.3 Deaths**

- Emergent adverse events leading to death (fatal as an outcome on the adverse event case report form page as reported by the Investigator) by primary SOC , HLGT, HLT, and PT showing number (%) of participants and the number (rate per patient-year) of AEs sorted by internationally agreed SOC order, with HLGT, HLT, and PT presented in alphabetical order within each SOC .
- Time to death will be compared in the randomized population with a baseline SPPB score <8 (as assigned by randomization) within the intervention arm, using a two-sided Log-rank's test stratified by study site and gender. Hazard ratio (and 95% CI) between intervention groups will be estimated using a Cox proportional hazard model with the stratification factors (study site and gender) as covariates. The cumulative incidence functions for the 2 intervention arms will be summarized using Kaplan-Meier method and displayed graphically. The cumulative incidence rate over time at each scheduled time-points of the protocol together with appropriate 95% confidence interval will be provided.

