## 10.2. Statistical analysis

Analyses of intervention effects will be based on the intent-to-treat principle. This implies that data from participants allocated to a treatment group will be analysed as part of that group irrespective of their compliance with treatment.

First approach analyses will always be dedicated to the evaluation of the subsample of participants with SPPB  $< 8$  (in agreement with results from the LIFE study and the present sample size calculations). Secondary analyses will subsequently be conducted considering the overall sample of the SPRINTT population (i.e.,  $n=1,500$ ) as well as the 300 participants with SPPB  $\geq 8$ .

All tests of significance will be two-sided with a maximal type I error risk of 5%.

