### **10.2.2. Secondary efficacy endpoints**

For the assessment of secondary efficacy endpoints, specific models will be used for continuous outcomes (e.g., changes in physical performance, nutritional status, functional status, cognitive function, and quality of life). Specifically, changes over time between groups will be assessed by a repeated-measure mixed model with terms for intervention, time, baseline score, baseline score by intervention interaction, and time by intervention interaction. For outcomes such as incidence of falls and mortality rate, the analysis defined for the primary efficacy outcome will be replicated (except for the secondary analysis with competitive risk for the mortality rate). Additional analyses (e.g., subgroup composite endpoint analyses) will be defined in agreement with the Managing Board and the Data Safety Monitoring Board and specified in the statistical analysis plan that will be produced prior to the beginning of the analyses.

Please note that within this section, we have limited the description of the analysis plan to the major SPRINTT hypotheses. Nevertheless, the relevance and amount of the data collected during the project will certainly lead to ancillary and secondary analyses always within the scopes and objectives of SPRINTT. Such secondary plans will be developed after formal approval and validation by the Managing Board of SPRINTT.

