### **2.1.4.3 Deaths**

The deaths observation period is from the date of randomization until the end of the study participation.

The safety endpoint mortality will also be assessed using the time from randomization to the date of death, as reported in an adverse event form by the investigator.

Participants not dead or lost to follow-up at the end of the study will be censored at the date of the study end or date of last news reported in the end-of-study form.

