## **2.2 DISPOSITION OF PARTICIPANTS**

This section describes participant disposition for both participant study status and the analysis populations.

Screened participants are defined as any participant who signed the informed consent.

Randomized participants consist of all participants with a signed informed consent form and who have been randomized by the system in one of the intervention arms, whatever the intervention attendance.

For participant study status, the total number of participants in each of the following categories will be presented in the clinical study report using a flowchart diagram or summary table:

- Screened participants
- Screen failure participants and reasons for screen failure as reported by the investigators in the inclusion criteria and exclusion criteria e-CRF pages
- Randomized participants
- Participants who completed the study (i.e. participants who were followed for at least 2 years)

- Participants who did not complete the study (i.e. participants who were followed for less than 2 years)
- Participants who discontinued study by main reason for study discontinuation

All categories of participants (except for the screened and nonrandomized categories) will be presented by intervention arm and the percentages will be calculated using the number of randomized participants within each intervention arm as the denominator. Reasons for study discontinuation will be supplied in a table giving numbers and percentages by intervention arm, as well as, displayed in a listing.

A summary of the distribution of participants by country and site will also be provided (overall number of patients screened, randomized, as well as number of participants who discontinued from study).

All critical or major deviations will be summarized in tables giving numbers and percentages of deviations by intervention arm.

Additionally, the following analysis study populations will be summarized by intervention arm.

- All randomized participants
- All randomized participants with a baseline SPPB score  $<8$  assigned by randomization
- All randomized participants with a baseline SPPB score  $\geq 8$  assigned by randomization

The discrepancy between randomization strata assigned by randomization (i.e. the baseline SPPB score and the sex) and the information reported on e-CRF will be summarized for all randomized patients

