## **2.3 ANALYSIS POPULATIONS**

The randomized population includes any participant who has been allocated to a randomized programme whatever the number of intervention attendance.

For any participant randomized more than once, only the data associated with the first randomization will be used in any analysis population. The safety experience associated with any later randomization will be assessed separately.

The main analysis population for all analyses (i.e. efficacy, safety and quality-of-life) will be the randomized population with a baseline SPPB score  $< 8$  as assigned by randomization. Participants will be analyzed according to the intervention arm allocated by randomization.

The secondary analysis population will include all randomized participants with a baseline SPPB score  $\geq 8$  as assigned by randomization and analyzed according to the intervention arm allocated by randomization.

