#### **2.4.5 Analyses of safety data**

The summary of safety results will be presented by intervention arm in the randomized population with a baseline SPPB score  $< 8$  assigned by randomization, and in the randomized population with a baseline SPPB score  $\geq 8$  assigned by randomization separately.

The “observation period” defined in [Section 2.1.4](#) is applicable to all safety analyses for the classification of AEs, determination of abnormality/potential abnormality values and the last on-study value for the laboratory and vital signs.

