#### **General common rules**

All safety analyses will be performed on the randomized population, using the following common rules:

- All the data from the randomization visit V1-T0 (or date of randomization if V1 is missing) will be considered in safety analyses

- For each safety parameter, the baseline for each participant is defined as the screening visit value or the randomization visit (V1-T0) value, whichever is the latest one.
- Abnormality/potential abnormality values are defined as values considered medically important according to predefined criteria/thresholds defined in the protocol for clinical laboratory test and vital signs [Appendix B and Appendix C])
- Abnormality criteria will determine which participants had at least one post-baseline abnormality during the emergent adverse event period, taking into account all evaluations performed during the study, including nonscheduled or repeated evaluations. The number of all such participants will be the numerator for the post-baseline abnormality percentage
- The post-baseline abnormality denominator by intervention arm for a given parameter will be based on the number of participants who have that parameter assessed during post-baseline assessments.
- All measurements, scheduled or withdrawal visit (V9), will be assigned to analysis windows defined in [Section 2.5.4](#) in order to provide an assessment for Month 3 to Month 36 time points.
- For quantitative safety parameters based on laboratory or vital signs measurements, descriptive statistics will be used to summarize results and change from baseline values by visit and intervention arm using analysis windows as defined in section 2.5.4.
- Summaries will include the last on-study value. The last on-study defined as the last available value collected at or just prior to the study end.

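### The SAP's only between-arm safety test, time to death, excludes 314 of 1,519 randomised participants (20.7%), and no pooled safety table is specified

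*Combined protocol and SAP*

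**What the plan says.** SAP 2.4.5.3 specifies a stratified two-sided log-rank test and a Cox hazard ratio for death, in one stratum only: "Time to death will be compared in the randomized population with a baseline SPPB score <8 (as assigned by randomization"). Nothing there repeats the test in SPPB ≥8 or in everyone. SAP 2.4.4.2 does extend the secondary efficacy analyses to SPPB ≥8, but mortality is not among the secondary efficacy endpoints in SAP 2.1.3.2.

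The rest of the safety section follows the same split. SAP 2.3 states: "The main analysis population for all analyses (i.e. efficacy, safety and quality-of-life) will be the randomized population with a baseline SPPB score" below 8, with SPPB ≥8 as the secondary population. SAP 2.4.5 adds: "The summary of safety results will be presented by intervention arm in the randomized population with a baseline SPPB score" below 8 and, separately, in those at 8 or above. SAP 2.4.5.1 takes the adverse event denominators from each stratum in turn.

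One line points the other way. The common rules under SAP 2.4.5 begin: "All safety analyses will be performed on the randomized population, using the following common rules". They name no pooled output.

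The ingredients for a pooled analysis exist. SAP 2.1.4.3 defines the endpoint without a stratum restriction: "The safety endpoint mortality will also be assessed using the time from randomization to the date of death". SAP 2.2 lists all randomised participants first under this sentence: "Additionally, the following analysis study populations will be summarized by intervention arm".

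Protocol 10.2 foresaw wider analyses: "Secondary analyses will subsequently be conducted considering the overall sample of the SPRINTT population". For mortality, protocol 10.2.2 says: "For outcomes such as incidence of falls and mortality rate, the analysis defined for the primary efficacy outcome will be replicated". That primary analysis (protocol 10.2.1) had a whole-population step, conditional on significance in SPPB <8. SAP 1.6 records no statistical modification.

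**The concern.** The trial randomises everyone to the same two programmes, yet its one formal comparison of harm covers only part of those randomised. SAP 1.3 explains the split by efficacy: in the earlier trial used for planning, the hazard ratio for mobility disability was 0.94 at SPPB ≥8 and 0.75 below 8. An expectation of little benefit in a stratum does not imply that harm there is uninteresting.

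Mortality is a secondary outcome in protocol 4.3.2. Protocol 11.9 names death among the rare serious events expected from the exercise programme. As written, the SAP yields no hazard ratio for death over all randomised participants. It also omits even the conditional whole-population step that protocol 10.2.2 would have carried over to mortality, without recording the change.

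**Working it through.** **Inputs.** SAP 1.3 gives 1,205 randomised with SPPB <8 and 314 with SPPB 8–9. The numbers at risk at time 0 in Figure S2 confirm the second figure: 155 + 159 = 314. Protocol 10.1 gives 434 events, 85% power, a hazard ratio of 0.75 and a two-sided 5% level. The documents give no planning death rate, so mortality (m), the relative death risk in SPPB 8–9 against SPPB <8 (r) and a target hazard ratio of 1.5 are assumptions, with m and r shown over ranges.

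**The plan's own figure.** Schoenfeld's formula with 1:1 allocation gives 4 × (1.960 + 1.036)² / (ln 0.75)² = 434 events, matching the protocol. The same formula is used below for deaths.

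**Share of people outside the hazard ratio.** 1,205 + 314 = 1,519, and 314 / 1,519 = 20.7%.

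**Share of deaths outside it, and precision.** The share of deaths is 314r / (1,205 + 314r). The standard error of the log hazard ratio is proportional to 1/√(deaths), so the ratio of pooled to SPPB <8 standard error is √(1,205 / (1,205 + 314r)). Neither depends on m.

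| r | Share of deaths outside | SE ratio | Fall in SE |
|---|---|---|---|
| 1 | 20.7% | 0.891 | 11% |
| 0.5 | 11.5% | 0.941 | 6% |
| 0.25 | 6.1% | 0.969 | 3% |

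**Power for a hazard ratio of 1.5, two-sided 5%.** Power = Φ(ln(1.5) × √D / 2 − 1.96), with D = 1,205m for SPPB <8 alone and D = 1,205m + 314mr pooled. For example, at m = 8%, D = 96.4 for SPPB <8 alone (51.2%) and 109.0 pooled at r = 0.5 (56.2%).

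| m in SPPB <8 | SPPB <8 alone | Pooled, r = 0.25 | Pooled, r = 0.5 | Pooled, r = 1 |
|---|---|---|---|---|
| 4% | 29.0% (D = 48.2) | 30.6% (51.3) | 32.1% (54.5) | 35.2% (60.8) |
| 8% | 51.2% (96.4) | 53.8% (102.7) | 56.2% (109.0) | 60.8% (121.5) |
| 12% | 68.4% (144.6) | 71.1% (154.0) | 73.6% (163.4) | 78.1% (182.3) |

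The gain runs from 30.6 − 29.0 = 1.6 points to 78.1 − 68.4 = 9.7 points.

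**The case against.** The strongest reply is that this is a consistent, pre-specified choice with a small consequence. Protocol 10.2 puts SPPB <8 first throughout, and the synopsis describes the SPPB 8–9 group as exploratory. That group still gets its own by-arm tables, fatal events included. Because patient-year rates are reported, a reader could build a rough SPPB-stratified death rate ratio from the two sets of tables. Protocol 11.9 sends monthly serious adverse event summaries by blinded arm to the monitoring board with no SPPB split stated, so oversight is not narrowed. Protocol 10.2.1 and 10.2.2 never promised an unconditional pooled mortality hazard ratio. A pooled estimate also assumes a common relative effect in a design that expects efficacy to differ by SPPB.

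Much of this stands. No death goes unreported, no bias arises and the primary inference is untouched. The 11% gain in precision needs people with SPPB 8–9 to die as often as the frailer stratum, which is unlikely.

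What does not follow is that the gap is filled. Monitoring summaries are not trial results. A hand-built rate ratio is not the site- and gender-stratified hazard ratio with its interval. Deaths in SPPB 8–9 do count as events in the whole-population primary analysis (SAP 2.1.3.1), but that analysis is conditional and does not estimate mortality. The common-rules wording can be read as meaning the as-randomised set reported by stratum, so it does not supply a pooled output.

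**Conclusion.** The point holds. The mortality test and hazard ratio cover 1,205 of 1,519 randomised participants (79.3%), and no pooled safety output is specified. The 20.7% left out is a share of people. The share of deaths left out is probably smaller: 6% to 21% if death risk at SPPB 8–9 is a quarter of, up to equal to, that below 8. The gain from pooling is modest, at 3% to 11% in standard error and about 2 to 10 points of power under the assumed mortality rates and a hazard ratio of 1.5. The case for change rests mainly on completeness: the only formal harm comparison should include everyone randomised. It is a worthwhile, low-cost correction that should be made, and the primary conclusion does not depend on it.

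**What to change.** In SAP 2.4.5.3, add a comparison of time to death in all randomised participants, using a log-rank test and Cox model stratified by site, gender and SPPB category. Run it regardless of the primary result, alongside the SPPB <8 analysis that protocol 10.2 puts first. In SAP 2.3 and 2.4.5, add all randomised participants as a safety population, with a corresponding column in the adverse event, serious adverse event, special-interest event, laboratory and vital-sign tables. Keep the by-stratum results as supportive, so that readers can judge the assumption of a common relative effect on death. Record the change in SAP 1.6.

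The cost is revised wording, one table column and one extra analysis. SPPB category is already a randomisation factor and no new data are needed. The primary type I error is unaffected, because SAP 2.4.4.3 controls it only for the primary endpoint. The one statistical price is the common-effect assumption behind the pooled hazard ratio.

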#### **2.4.5.4 Analyses of laboratory variables**

Laboratory parameters will be grouped and summarized by biological function as described in Section 2.1.4.4. The summary statistics (including number, mean, median, SD, minimum and maximum) of all laboratory variables (values and changes from baseline) will be calculated for each visit or study assessment (baseline, each post baseline time point, last on-study) by intervention arm.

For baseline hematology and clinical chemistry parameters, the number and percentage of participants with normal value, out of range value, potentially medically important value and value requiring immediate notification, according to the thresholds defined in the protocol (list provided in Appendix C).

The total number and percentage of participants presenting at least one post-baseline abnormality as defined in the protocol will be presented by intervention arm, irrespective of the baseline level and according to the following baseline categories:

- Normal/missing
- Abnormality criteria as defined in the protocol

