| No posterior tibial arterial signal present in either leg                                                                                                                                  | The participant will be examined by a qualified staff member who will evaluate the participant for                                                                                                                                                                                        |

|                                                                                  |                                                                                                                                                                                                                                                                                                                                     |
|----------------------------------------------------------------------------------|-------------------------------------------------------------------------------------------------------------------------------------------------------------------------------------------------------------------------------------------------------------------------------------------------------------------------------------|
|                                                                                  | signs of critical limb ischemia. The qualified staff member will re-check for presence of a posterior tibial artery signal and will check for presence of a dorsalis pedis arterial signal. Appropriate follow-up will be recommended. If critical limb ischemia is determined to be present, the study physician will be notified. |
| Serum glucose <60 during intervention session in diabetic on hypoglycaemic agent | Intervention staff provide immediate care such as offering beverage with sugar and advise participant to contact primary care physician regarding adjustment of hypoglycaemia medication                                                                                                                                            |

The following cut-points will be used to determine abnormal values for blood tests:

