**2.4.5.5 Analyses of vital sign variables**

The summary statistics (including number, mean, median, standard deviation, minimum and maximum) of all vital signs variables (SBP, DBP, HR and changes from baseline) will be calculated for each study assessment (baseline, each post-baseline time point, last on-study) by intervention arm. For these parameters mean changes from baseline with the corresponding standard error will be plotted over time (at same time points) in intervention arm.

The total number and percentage of participants presenting at least one post-baseline abnormality in SBP, DBP or HR, as per the threshold defined in the protocol (list provided in Appendix B) will be presented by intervention arm, irrespective of the baseline level and according to the following baseline categories:

- Normal/missing
- Abnormality criteria as defined in the protocol

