***Handling of laboratory and vital signs abnormalities***

If a participant has a missing baseline he will be grouped in the category “normal/missing at baseline.”

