**Appendix B    Vital signs abnormalities and alert**

| ALERT                                          | ACTION                                                                                                         |
|-------------------------------------------------------|-----------------------------------------------------------------------------------------------------------------------|
| Blood Pressure
SBP > 140mm/Hg or
DBP > 90mm/Hg  | Clinic staff inform the participant                                                                                   |
| Blood Pressure
SBP > 170mm/Hg or
DBP > 100mm/Hg | Qualified staff should talk to participant, and encourage participant to seek additional follow-up and/or evaluation. |
| Resting Pulse
Rate > 100 or < 40 beats/min         | Qualified staff should talk to participant, and encourage participant to seek additional follow-up and/or evaluation. |

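### The planned abnormality counts for laboratory tests and pulse name neither direction nor severity tier, so a new low value after a high baseline has no count of its own by arm

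*Combined protocol and SAP*

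**What the plan says.** For laboratory tests, SAP 2.4.5.4 asks for this count: "The total number and percentage of participants presenting at least one post-baseline abnormality as defined in the protocol will be presented by intervention arm". It is to be shown "irrespective of the baseline level and according to the following baseline categories". The first category pools normal and missing baselines. The second is worded only as "Abnormality criteria as defined in the protocol". Section 2.5.3 confirms the pooling: for a participant without a baseline value, "he will be grouped in the category “normal/missing at baseline".

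SAP 2.4.5.5 uses the same layout for vital signs and counts participants "presenting at least one post-baseline abnormality in SBP, DBP or HR, as per the threshold defined in the protocol".

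The general rules in SAP 2.4.5 give the definition: "Abnormality/potential abnormality values are defined as values considered medically important according to predefined criteria/thresholds defined in the protocol". They refer to Appendices B and C. They also say that every evaluation during the study counts, including unscheduled and repeated ones.

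Appendix C has three columns of rising severity: out of reference range, potentially medically significant, and requiring immediate notification. For glucose the limits are below 70 or above 125, below 60 or above 140, and below 50 or above 400 mg/dL. Each pair stands in one cell. Appendix B treats pulse in the same way: "Rate > 100 or < 40 beats/min".

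SAP 2.4.5.4 does ask for the full severity grading (normal plus three tiers), but for baseline values only.

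**The concern.** An abnormality that can lie on either side of the normal range is two different findings. If the two are counted as one, fewer highs in one arm can offset more lows in the same arm. A participant who already has a high value adds nothing to the count when a low value appears later. Exercise and dietary counselling could plausibly move glucose or pulse in one direction, so direction is what a safety reader would want to see.

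Leaving the tier open adds a second problem. Two programmers could build different tables from the same text, and a mild excursion after baseline is not separated from one that required immediate notification.

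**Working it through.** The documents state no figure on this point, so there is nothing to reproduce. The check applies the written criteria to cases.

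**1. How many criteria are two-sided?** Appendix C lists 14 tests.
- Two-sided (7): haemoglobin, white cells, platelets, sodium, potassium, calcium, glucose.
- One-sided (7): triglycerides, total cholesterol, HDL, urea nitrogen, creatinine, albumin, vitamin D.
- In Appendix B, pulse is two-sided. Systolic and diastolic pressure have upper limits only.

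**2. What does the table record?** Rule as written: abnormal = (value < lower limit) or (value > upper limit). Each participant is classed by baseline (abnormal or not) and by whether any post-baseline value is abnormal.

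**3. Glucose, with example values in mg/dL and the Appendix C limits.** Each cell shows baseline status, then post-baseline status.

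| Baseline, later value | Out of range (<70 or >125) | Potentially significant (<60 or >140) | Immediate notification (<50 or >400) |
|---|---|---|---|
| 150, 150 | abnormal, abnormal | abnormal, abnormal | normal, not abnormal |
| 150, 45 | abnormal, abnormal | abnormal, abnormal | normal, abnormal |
| 130, 55 | abnormal, abnormal | normal, abnormal | normal, not abnormal |
| 100, 45 | normal, abnormal | normal, abnormal | normal, abnormal |
| 100, 150 | normal, abnormal | normal, abnormal | normal, not abnormal |

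Three things follow.
- Rows 1 and 2 are identical at the two lower tiers: a persistent high and a new low share a cell. They differ only at the top tier, where a baseline of 150 counts as normal and the 45 is therefore new.
- Rows 4 and 5 are also identical at the two lower tiers, so direction is lost in the normal-baseline row too.
- Row 3 lands in a different cell under each tier, so the table depends on a choice that the SAP does not make. The phrase about medical importance in the general rules suggests a tier above the first but does not name one.

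**4. Repeated values.** Because every evaluation counts, one later high value is enough to place a participant in the numerator. A low value at another time then leaves the count unchanged.

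**5. Do other planned outputs supply the missing count?**
- *Visit summaries.* The minimum is one number per arm and visit, not a number of participants, and it is not linked to baseline status. The largest fall from baseline need not end in a low value. SAP 2.5.4 keeps only the value nearest the target day in each window, so an additional low value can drop out. The abnormality count is the output whose rule expressly admits unscheduled values.
- *Adverse events.* SAP 2.1.4.1 limits collection to four classes. A laboratory result becomes an event of special interest only if it requires immediate medical attention. Preferred-term coding would then ordinarily show its direction, but lower-grade lows need not appear.
- *Baseline severity table.* It has tiers, but no direction and no post-baseline counterpart.

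**The case against.** The strongest reply is that the SAP never says the two directions are merged. Separating the two sides of a limit is compatible with its wording and could be settled in the table shells. That is correct: the defect is an unspecified direction and tier, and merging is the literal reading rather than a stated rule. The tables are also descriptive, with no test or decision rule attached, and half of the Appendix C tests are one-sided and unaffected.

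Four stronger readings are tempting, and the documents do not support them.
- *That a new low after a high baseline is set aside as pre-existing.* It is not. The participant stays in the abnormal-at-baseline row and in the total irrespective of baseline, by arm.
- *That the arms cannot be compared on low values at all.* Visit minima, changes from baseline, coded adverse events and, if it were the tier used, the immediate-notification limit all carry some information by arm.
- *That the table hides low glucose during exercise.* The alert in protocol 11.4, "Serum glucose <60 during intervention session in diabetic on hypoglycaemic agent", concerns intervention sessions. Laboratory samples under SAP 2.1.4.4 are taken at randomisation, months 12, 24 and 36 and, if applicable, the end-of-study visit. In-session events belong to the supervised-event and special-interest reporting, and splitting this table would not capture them.
- *That the dilution of a difference between arms can be put in numbers.* That needs the proportion high at baseline, the proportion with further high values and the rate of lows in each arm. The documents give none of these.

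These points narrow the concern. They do not supply a count of participants by direction.

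**Conclusion.** The point holds in this limited form. For seven of 14 laboratory tests and pulse, the planned abnormality table has no direction. For the laboratory tests it has no named tier and no post-baseline severity grading either. At two of the three glucose tiers, a new low in a participant who was high at baseline cannot be told apart from a persistent high. Other planned outputs replace the missing count only in part.

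The conclusion rests on reading each joined limit as a single criterion, and on the tables being programmed from the SAP text without further specification. How many participants are affected is unknown. No efficacy conclusion depends on it. It is a worthwhile and inexpensive improvement to the safety reporting.

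**What to change.** Leave all Appendix B and C thresholds as they are and amend the SAP as follows.

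1. In 2.4.5.4 and 2.4.5.5, count the low and the high side of each two-sided criterion separately by arm. A participant with both counts once on each side.
2. Class baseline as low, normal, high or missing. This also means changing the rule in 2.5.3 that joins missing with normal.
3. For laboratory tests, state which Appendix C tier defines an abnormality, and tabulate the worst post-baseline tier in each direction against baseline status.
4. Keep the existing rules on denominators and on including unscheduled values.

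No new data are needed. The cost is table length. A two-sided test now takes 3 rows (the total and two baseline categories). With a total and four baseline classes on each side it takes 2 × 5 = 10, with the tiers as columns. Over the seven laboratory tests that is 7 × 3 = 21 rows becoming 7 × 10 = 70, in each SPPB stratum, plus the pulse rows.
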